### End of study

All patients will be followed up to collect data on their status at 4 months postoperation. If contact cannot be made or data collected within 3 months of this point, follow-up will not be collected. After the 4-month follow-up, participants will be treated as per normal standard of care with no further study-specific follow-up.

### Data collection and data management

Personal data collected during the trial will be handled and stored in accordance with the 1998 Data Protection Act and CTU Standard Operating Procedures.

The data collected from participants will be entered in the study and NHFD databases. All data collected will be anonymised after the collection of the baseline demographic data and all participants given a unique study number. Identifiable participant data will be held on a separate database and in a locked filing cabinet and coded with a study participant number to tag identifiable data to the outcome data.

With the patient's consent, data may be linked to routine NHS and social care data sets via the Health and Social Care Information Centre or appropriate body.

Disclosure of confidential information will only be given if a participant indicates an issue that may jeopardise the safety of the participant or another person.

### Oversight Committee

The Oversight Committee comprises of representatives from each of the professional groups involved in the care of patients with hip fracture and lay representatives of the patient group. They will collectively manage the data governance arrangements, although final responsibility will lie with the chief investigator.

## Data analysis

### Observational studies

The WHiTE framework will be suitable for addressing a broad range of hip fracture research questions, either alone or in concert with national data from its parent registry, the NHFD. It will not be suitable for studies relating to younger adults with hip fractures or those treated non-operatively. An illustrative list of the types of research question for which WHiTE may be suitable includes:

*Descriptive epidemiology*: Describing the occurrence and distribution of hip fractures in the UK, for example, is there an association between socioeconomic status and outcome, including loss of health-related QoL, after hip fracture?

*Health services research*: Exploring the effects of differences in healthcare delivery, for example, does hospital hip fracture volume affect patient outcomes?

*Outcome studies*: Studying the impact of treatment decisions on patients, for example, does compliance with NICE guidelines improve outcomes for patients with hip fractures?

The Oversight Committee will prioritise individual study ideas and manage the application process for using WHiTE data. They will prospectively approve study applications in advance of any data being shared or analysed.

### Sample size

A sample size for a study such as the one we propose here is difficult to determine with any degree of precision. This is, in large part, due to the flexibility of the approach being adopted, that is, specific research questions will be identified by the Oversight Committee over time.

However, there are aspects that are determined a priori that can guide an initial sample size. A key determinant of the sample size, and also an important outcome in itself, in this frail (elderly) population is the death rate. Previous analyses^5^
^13^ have shown that the death rate in this group is between 20% and 30% at 12 months, but data were sparse and limited. One research question that we know will be important is to establish the overall population death rate and model how it changes in the immediate postoperative period. Table 1 shows 95% CIs for estimates of death rates of 20% and 30% for varying sample sizes (n), based on a binomial model.

**Table 1 BMJOPEN2016011679TB1:** CIs (95%) for death rates of 20% and 30% by sample size (n)

	Death rate	
n	20%	30%
100	(12.9 to 29.4)	(21.5 to 40.1)
300	(15.7 to 25.1)	(24.9 to 35.6)
1000	(17.6 to 22.6)	(27.2 to 33.0)
3000	(18.6 to 21.5)	(28.4 to 31.7)
6000	(19.0 to 21.0)	(28.8 to 31.2)

In order to estimate the death rate to a high level of precision (within 1%), a reasonable target overall sample size is therefore ∼6000 participants. The death rate is likely to vary within important subgroups of the population (eg, fracture type), so it is also important to consider the precision of estimation of the death rate within the smallest clinically important subgroup, which we think is likely to be in the order of 5% of the overall population. Based on 6000 participants, this amounts to a subgroup of 300, and a CI of ∼10% for estimating the death rate.

Formal analyses will be undertaken, after identification of important research questions by the Oversight Committee, using multiple regression analyses with QoL (EQ-5D) as the response variable. Therefore, Cohen's f^2^ provides a useful way for characterising the probable effect size when fitting such models for continuous outcomes.^17^ Sticking with the above setting, and the smallest clinically important subgroup (n=300) indicates that we will have 95% and 75% power to detect an effect size of 0.08 and 0.05, respectively, at the 5% level in this population and assuming we use 10 degrees of freedom for model fitting. Typical values of f^2^ of 0.02 and 0.15 represent small and moderate effects sizes, so values in the range 0.05–0.08 are small to moderate. Cohen's f^2^ is determined by the ratio of the proportion of variance accounted for in the multiple regression model (regression R^2^ value) to one minus that proportion. Experience suggests that R^2^ values are often small (10–20%) in the setting described here, as QoL is very variable and much of the variability will not be captured by the small number of explanatory variables we will have available for model fitting. Nevertheless, even if models account for only 10% of the variance in QoL we should still have considerable power (>80%) to address important regression relationships within our subgroups of size 300, even allowing some reduction in this number for loss to follow-up.

In summary, an initial sample size of 6000 patients will provide considerable power to estimate overall population characteristics such as death with a high level of precision. Assuming that we are interested in clinically significant subgroups no smaller than 5% of this total (n=300) we will have good power to detect small to moderate effects sizes in our planned multiple regression analyses. On average, each of the WHiTE recruitment sites treats 500 patients with hip fracture a year (range 300–700; NHFD reports) and so we anticipate reaching the 6000 patient sample in 2017.

It is anticipated that the data generated by the cohort study will be used to support and inform hypotheses that are suggested by clinical practice. The Oversight Committee will decide whether any interim analyses are necessary to inform future questions in order to prevent repeated attempts to interrogate the data set without a priori hypotheses. The cohort study data will also be used to update estimates of ‘nuisance’ parameters, such as the death rate and QoL variability in the study population. These nuisance parameters will be used to refine estimates of sample sizes for future embedded randomised controlled trials.

An example observational study within the WHiTE observational cohort might investigate whether the type of fracture a patient sustains influences the patient's outcome. While the optimal interventions for each fracture pattern are defined in current guidelines, the effect of fracture pattern on patient outcome is not well understood. Data from the NHFD 2014 report (n=64 838) give a breakdown of fracture types as follows: undisplaced intracapsular 9.5% (n=6165), displaced intracapsular 48.8% (n=31 656), trochanteric 34.6% (n=22 422), subtrochanteric 5.4% (n=3507) and not specified 1.7% (n=1088). Suppose we were interested in understanding the relationship between the type of intervention, anaethestic and rehabilitation within the subtrochanteric fracture subgroup. This subgroup comprises ∼5.4% (n=325) of the study population (n=6000). Let us assume 90% follow-up rates at 4 months (ie, n is ∼300), with EQ-5D as the primary outcome, and the definitive analysis is a multiple linear regression adjusting for age and gender as minimum. Taking a conservative estimate of R2^5^
^13^ to give a value of Cohen's f^2^ of 0.05, suggests that we will have 85% power to detect a statistically significant regression analysis, at the 5% level, in the smallest subgroup of interest (subtrochanteric fractures) for a sample size of 300 patients. A 4-month follow-up rate of >90% is anticipated based on a WHiTE pilot study, which successfully followed up 88% of patients at 12 months.^5^

Analogous economic burden and health economic assessments will be integrated into the analysis plan for each observational study. The economic assessments will be conducted from the recommended NHS and personal social services perspective.

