## Patients and methods

### Eligibility

All patients presenting with a hip fracture to one of the recruiting National Health Service (NHS) sites and who would currently be reported to the NHFD. Alignment with the NHFD eligibility criteria will reduce the data collection burden at recruiting sites, which is important for its sustainability as further studies are embedded within the WHiTE framework. The NHFD exclusion criteria are:
Age <60 years.Non-operative treatment.^7^

Throughout the study, screening logs will be kept to determine the number of patients assessed for eligibility and reasons for any exclusion. Patients who decline to consent to take part will be given the opportunity to inform the research team of the reasoning behind their decision not to participate.

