### Consent

Patients with a hip fracture are a clinical priority for urgent operative care and will usually undergo surgery on the next available trauma operating list. All WHiTE recruiting sites treat hip fracture patients according to national guidelines and so patients will be managed according to a series of common standard treatment pathways. The WHiTE study will not affect their treatment in any way. The patients will be approached for consent to be part of this cohort study in the immediate postoperative period.

At the first appropriate time when the patient has regained capacity (usually the first day after surgery) a research associate will provide the participant with the study information. The patient will be given the opportunity to ask questions and discuss the study with their family and carers for as long as they require. They will then be asked to provide written consent to participate in the study. If the patient does not wish to complete questionnaires for the study at this stage, they will be asked if they are happy to provide written consent for us to access and use any routine NHS data, including that collected through the NHFD. Alternatively the patient can choose to decline to have any data entered into the study.

Best efforts will be made to involve participants who, temporarily or permanently, lack capacity in the decision to be involved in the study. The clinical team will make a judgement about the amount and complexity of the information that the participant is able to understand and retain on an individual basis. Appropriate information will be communicated to the participant and updated as their understanding changes. In the event that a patient has temporary loss of capacity, we will follow best practice and ask the patient for consent as soon as they are able to do so.

In accordance with section 32 subsection 9b of the Mental Capacity Act 2005, where a patient does not have capacity to consent for themselves, we will seek agreement from an appropriate consultee.

Where a personal consultee is available, they will be provided with the study information. The personal consultee will be given the opportunity to ask questions and discuss the study after which they will be asked to provide agreement, which will be documented. The personal consultee will complete the outcome questionnaires on behalf of the patient.

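### Enrolment only after surgery turns the planned population death rate into mortality among patients who survive to enrolment: biased downward, most at the start of the curve, by an amount the protocol does not determine

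*Protocol article*

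**What the plan says.** Sample size (protocol article, Data analysis) treats the death rate as a key determinant of the sample size and as an outcome in its own right. The aim is to "establish the overall population death rate and model how it changes in the immediate postoperative period". The anticipated value comes from earlier analyses, in which "the death rate in this group is between 20% and 30% at 12 months". Table 1 gives 95% intervals "based on a binomial model"; at n=6000 they are 19.0 to 21.0 for a rate of 20% and 28.8 to 31.2 for 30%. The target of about 6000 follows from wanting precision within 1%.

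Consent fixes when a patient can enter: "The patients will be approached for consent to be part of this cohort study in the immediate postoperative period". This is usually the first day after surgery for a patient who has regained capacity. For others, "where a patient does not have capacity to consent for themselves, we will seek agreement from an appropriate consultee". A patient may also decline to have any data entered.

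Eligibility excludes patients under 60 and those treated non-operatively, and states that "screening logs will be kept to determine the number of patients assessed for eligibility and reasons for any exclusion". The Observational studies section discloses that the framework does not suit questions about younger or non-operated patients. It says nothing of operated patients who die before being approached.

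**The concern.** Everyone in the cohort is, by construction, alive from operation until consent or consultee agreement. Deaths in that interval are in neither the numerator nor the denominator. The quantity named in Sample size belongs to the whole operated population and includes the immediate postoperative period, which is where the cohort has a gap.

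For this mechanism the direction is certain: the death rate is understated, and the early part of the curve is understated most. A larger sample does not help, because it only narrows the interval around a shifted value. The estimate also travels further: Sample size says the cohort's death rate will be used to refine sample sizes for future embedded randomised trials. The gap cannot be left wholly to a later analysis plan, because deaths that nobody counted at the sites cannot be recovered from the cohort data.

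**Working it through.** **1. The plan's own precision figure.** Half-width = 1.96·√[p(1−p)/6000]:
- p = 20%: 1.01 points
- p = 22.5%: 1.06 points
- p = 30%: 1.16 points

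A Wilson score interval with continuity correction reproduces all ten intervals in Table 1 to 0.1 point. The stated precision is arithmetically sound, although at 30% it is slightly wider than 1 point.

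**2. The bias.** Let p be the death rate among all eligible operated patients and e the fraction dying between operation and entry.
- Rate seen among enrolled patients: (p−e)/(1−e)
- Bias: p − (p−e)/(1−e) = e(1−p)/(1−e), downward

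**3. What a 1-point bias requires.** Setting the bias to 0.01 gives e = 0.01/(1−p+0.01). The Introduction gives 8.5% mortality within 30 days of injury, which puts e in context:

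| p | e needed | e as a share of the 8.5% |
|---|---|---|
| 20% | 0.01/0.81 = 1.23% | 14.5% |
| 22.5% | 0.01/0.785 = 1.27% | 15.0% |
| 30% | 0.01/0.71 = 1.41% | 16.6% |

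**4. Plausible sizes.** The protocol does not give e, so these are assumptions. They use the Introduction's 8.5% at 30 days and 22.5% at 12 months, with entry at day 1 or 2. Bias ranges cover p from 20% to 30%.

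*(a) Constant hazard over 30 days, clock from injury.* h = −ln(0.915)/30 = 0.00296 per day.
- Day 1: e = 0.30%, bias 0.21–0.24 point
- Day 2: e = 0.59%, bias 0.42–0.48 point
- The bias passes 1 point across the whole range of p only with entry at about day 5 (e = 1.47%, bias 1.04–1.19)

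*(b) Front-loaded Weibull through both mortality figures, clock from injury.* Shape = ln[ln(0.775)/ln(0.915)]/ln(365/30) = 0.42.
- Day 1: e = 2.09%, bias 1.5–1.7 points
- Day 2: e = 2.79%, bias 2.0–2.3 points

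*(c) The same Weibull, counting only deaths after surgery, with surgery on day 1 and entry on day 2.* e = (2.79−2.09)/(100−2.09) ≈ 0.7%, bias 0.5–0.6 point.

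Some front-loading is credible. The two mortality figures imply an average daily hazard of 0.0888/30 = 0.00296 up to day 30 and (0.2549−0.0888)/335 = 0.00050 afterwards, about a sixfold difference. They do not say how deaths fall within the first few days.

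**5. Effect on the interval at n=6000.** A bias of 0.47 point lowers the coverage of a nominal 95% interval to about 85% (p = 20%) or 87% (p = 30%). A bias of 1 point lowers it to about 49% or 60%.

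**6. Early mortality.** At p = 8.5% the half-width is 1.96·√(0.085·0.915/6000) = 0.71 point. A bias of that size needs e = 0.0071/(0.915+0.0071) = 0.77%, or about 9% of the 30-day deaths. Before the first enrolments, no cohort member is under observation at all.

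**7. Whether the text closes the gap elsewhere.**
- Consultee agreement brings in living patients without capacity. It is not described as a route for someone who has already died.
- The screening logs record reasons for exclusion, but death before approach is not named as a reason or added to a denominator.
- Validation compares the cohort with the NHFD and other data sets once 6000 are enrolled. Its only example is age structure.

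**The case against.** The strongest reply is that the size is unknown and the means to deal with it are largely in place. The only stated timing is usually the first day after surgery, which at constant hazard gives about 0.2 point. The cohort is nested in the NHFD, may be analysed together with national NHFD data, keeps screening logs and plans external validation. Study-specific analysis plans are foreseen. All of this is true, and it makes the remedy cheap. But none of these provisions is tied to deaths before approach, and the entry rule and the target quantity are both fixed in this document.

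A reader might infer several stronger things that the documents do not support:
- *That the bias is about as large as the claimed 1-point precision, or larger.* This depends on the undocumented share e. The scenarios fall on both sides of 1 point. Moreover, 8.5% is counted from injury in all hip fracture patients. Running it from operation counts pre-operative and non-operated deaths as missed, although those lie outside the disclosed scope.
- *That the death rate will be analysed as a simple binomial proportion.* The binomial model is given only for the Table 1 precision figures. The change in the death rate is to be modelled by a method not named.
- *That patients without capacity are lost.* The consultee route covers them while they live.
- *That sites consenting later will look safer.* This is possible in principle, but the protocol gives no consent timing by site.

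Refusal may add further selection, of unknown direction.

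**Conclusion.** The conflict between the target quantity and the entry rule stands. As written, the cohort can estimate mortality only among operated patients who survive to enrolment. It understates the rate for all operated patients, and it cannot show the start of the postoperative curve. The stated interval does not reflect this.

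The size is conditional. It is 1 point at p of 20–30% only if about 1.2–1.4% of operated patients die before entry. Assuming entry at day 1–2, it lies between about 0.2 and 2.3 points: 0.2–0.5 under constant hazard, and 0.5–2.3 under the front-loaded curve, depending on when surgery falls. The figures from 1.5 points upward count from injury and tend to overstate the bias for operated patients. The direction is firm; the magnitude rests on assumed timing and hazard shape. The point concerns the death-rate question. It does not show that the planned EQ-5D regressions are wrong.

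**What to change.** - **Count the missing deaths.** Add death between operation and approach as a category in the screening logs already kept, or obtain aggregate NHFD deaths for all eligible operated patients at the recruiting sites. Report the population death rate and the early curve on that denominator, and state how many died before approach. This is the essential step.
- **Within-cohort survival analyses.** Take the date of operation as time origin, with delayed entry at consent or consultee agreement. Say plainly that this cannot recover the hazard before the first entries. It also assumes entry time is unrelated to risk, which is doubtful when entry waits on regained capacity.
- **If neither count is obtained,** label the estimate as the *death rate among operated patients surviving to enrolment*, and drop the claim to the overall population rate.

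The cost is one log category or one aggregate extract, plus a sentence in Sample size. Recruitment does not change.

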## Introduction

The World Hip Trauma Evaluation (WHiTE) project was set up to measure outcome in a comprehensive cohort of UK patients with hip fracture. All patients in the cohort are treated under a single comprehensive treatment pathway. A core outcome set, including health-related quality of life (QoL), is collected on all the patients.

This protocol describes the current multicentre project that will be used as a vehicle to deliver a series of embedded observational studies.

Osteoporotic hip fractures present a significant global challenge to patients, clinicians and healthcare systems. It is estimated that hip fracture accounts for 1.4% of total social and healthcare costs in the established market economies.^1^ Approximately 8.5% of patients with hip fracture will die within 30 days of injury^2^ and 22.5% within 12 months.^2^
^3^ In addition, the majority of survivors experience a significant reduction in health-related QoL.^4^
^5^ The challenge is expected to intensify with a rise from the 1.3 million hip fractures in 1990 to 6.3 million globally by 2050.^6^

The National Hip Fracture Database (NHFD) already captures data on almost all patients with hip fracture in England, Wales and Northern Ireland.^7^ Although it is used principally for national clinical audit, there is considerable potential to use the NHFD for research purposes.^3^ However, the NHFD does not routinely capture patient-reported outcome measures and there is substantial variation in clinical decision-making (eg, choice of fixation device) between hospitals and individual surgeons, which risks introducing confounding to observational studies embedded within the NHFD.^8^

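### The ±1-point precision for the population death rate treats patients in a multicentre cohort as independent, and the minimum regression model names no hospital effect

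*Protocol article*

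**What the plan says.** All references are to the protocol article.

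- **Precision (Sample size).** Earlier analyses are cited as showing that "the death rate in this group is between 20% and 30% at 12 months". Table 1 gives 95% intervals "based on a binomial model". At n=6000 they are 19.0 to 21.0 (20% rate) and 28.8 to 31.2 (30% rate). To estimate the rate within 1%, "a reasonable target overall sample size is therefore" about 6000. The quantity of interest is described as the overall population death rate.
- **Power (Sample size).** The smallest important group is 5% of the total: "this amounts to a subgroup of 300". Formal analyses will be done "using multiple regression analyses with QoL (EQ-5D) as the response variable". Power is put at 95% for f²=0.08 and 75% for f²=0.05, with 10 model degrees of freedom whose content is not stated. The worked example on subtrochanteric fractures names age and gender as the minimum adjustment.
- **Hospitals.** The Introduction notes "substantial variation in clinical decision-making (eg, choice of fixation device) between hospitals and individual surgeons" and calls this a confounding risk for studies embedded in the national registry, within which this cohort is nested. The response is a common guideline-based pathway, expected to help limit the variability. Under Standardised treatment pathway, antibiotics, thromboprophylaxis and nerve blocks still follow centre or local protocols. Under Observational studies, one listed question is "does hospital hip fracture volume affect patient outcomes".
- **Not stated.** The Sample size section gives no number of sites, ICC or design effect. Sites treat on average 500 hip fractures a year (range 300 to 700).

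**The concern.** Patients treated in the same hospital share case mix, staff and local policy, so their outcomes are likely to be correlated. With hundreds of patients per site, even a very small correlation inflates the variance of an overall rate. The 6000 target rests on the ±1-point claim, so this affects the figure the document uses to justify its size.

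Two further consequences follow for the regressions. For an exposure that is constant within a hospital, such as volume, the information depends mainly on the number of hospitals, and standard errors that treat patients as independent would be too small. For an exposure partly set by local policy, such as a nerve block, an analysis with only the named minimum covariates could mix the effect of the exposure with other features of the hospital.

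**Working it through.** **1. Reproducing the stated figures.** A continuity-corrected Wilson interval for a simple binomial matches all ten intervals in Table 1 to the decimal. For power, the overall F test with u=10, v=300−10−1=289 and noncentrality f²×300 gives 93.8% at f²=0.08 (stated 95%) and 74.3% at f²=0.05 (stated 75%). Both calculations therefore use independent patients, with no hidden allowance for clustering.

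**2. Death-rate precision under independence.** Half-width = 1.96×√(p(1−p)/6000).
- p=0.20: 1.96×√(0.16/6000) = 1.01 points.
- p=0.30: 1.96×√(0.21/6000) = 1.16 points, shown as 1.2 in Table 1.

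So the 1-point target has no slack at 20% and is already missed at 30%.

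**3. With clustering.** Design effect DE = 1+(m−1)×ICC, where m = 6000/(number of sites) and sites are taken as equal in size. The half-width is multiplied by √DE. Site number and ICC are assumptions.

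| Sites (m) | ICC | DE | Half-width at 20% | Half-width at 30% |
|---|---|---|---|---|
| 10 (600) | 0.001 | 1.60 | 1.28 | 1.47 |
| 10 (600) | 0.01 | 6.99 | 2.68 | 3.07 |
| 12 (500) | 0.001 | 1.50 | 1.24 | 1.42 |
| 12 (500) | 0.005 | 3.50 | 1.89 | 2.17 |
| 12 (500) | 0.01 | 5.99 | 2.48 | 2.84 |
| 30 (200) | 0.001 | 1.20 | 1.11 | 1.27 |
| 30 (200) | 0.01 | 2.99 | 1.75 | 2.01 |

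At 12 sites and ICC 0.01, the 6000 patients carry the information of 6000/5.99, or about 1000.

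To judge the ICC range: the between-hospital SD of the rate is √(ICC×p(1−p)). At p=0.20, ICC 0.001 is √0.00016 = 1.3 points and ICC 0.01 is √0.0016 = 4.0 points.

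**4. Regression power in the subgroup of 300, patient-level covariates.** Adding hospital indicators for 10 to 30 sites removes 9 to 29 residual degrees of freedom. With partial f² unchanged:
- f²=0.05: from 74.3% to 72.7%–68.7% if the noncentrality is scaled to the reduced degrees of freedom, or essentially unchanged at about 74% if it stays at f²×300.
- f²=0.08: from 93.8% to 93.0%–90.7%, or about 94%.

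The loss is about 0 to 6 points.

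**5. Hospital-level exposures.** With 10 to 30 hospitals there are only 9 to 29 between-hospital degrees of freedom, however many patients are recruited.

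**The case against.** The article describes a framework. Questions are chosen and approved study by study, and it refers to an analysis plan for each study. Covariates, random effects and variance estimators normally belong there. Four stronger readings are therefore not supported:

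- *The regression has no hospital term.* Age and gender are only a minimum and the 10 degrees of freedom are unspecified. The text shows only that no hospital effect is named.
- *Hospital confounding is left in.* The confounding remark concerns registry-embedded studies in general, and the common pathway is the stated response. It standardises the type of fixation device for trochanteric and subtrochanteric fractures, and device choice is the Introduction's own example. Since local protocols and surgeon discretion remain for other items, confounding may remain; the text does not show that it does.
- *Power in the subgroup of 300 falls to 62% or 34%.* These values come from applying the full design effect (12 sites, m=25, ICC 0.01 and 0.05, f²=0.05) to all 10 degrees of freedom, as if every covariate were constant within hospital. The worked example concerns patient-level variables, for which step 4 is the relevant calculation.
- *The intervals are too narrow whatever the target.* That requires a positive ICC and inference beyond the recruited hospitals. With the sites taken as fixed strata, the binomial interval would not be too narrow.

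It is also fair that hospital volume is one item in an illustrative list, possibly to be studied together with national registry data, and that no sample-size claim is made for it. Table 1 does state its model, and 6000 is called an initial figure.

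These points narrow the concern but do not remove it. Table 1, the 6000 target, the power statements and the minimum adjustment set are fixed in this document. The stated target is a population rate, and the Validation section aims to relate the cohort to the wider UK hip fracture population, which goes beyond the recruited sites.

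**Conclusion.** The point holds in limited form. The stated precision and power are independent-patient calculations, confirmed by reproduction, and the minimum model names no hospital effect although the document itself identifies hospital variation and lists a hospital-level exposure.

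The material consequence is for the overall death rate. At a 20% rate the half-width is about 1.1 to 1.3 points at ICC 0.001 and 1.75 to 2.7 points at ICC 0.01, not 1.0. This rests on four assumptions: 10 to 30 sites, equal site sizes, the stated ICC values, and inference beyond the recruited hospitals. The documents supply neither the site number nor the ICC, so the size can only be a range. The figure of 500 patients per site-year makes 6000 equal to 12 site-years, which is not the same as 12 sites.

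For patient-level regressions in the subgroup of 300 the effect on power is small. For hospital-level exposures, neither 300 nor 6000 is the relevant sample size.

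**What to change.** - Label Table 1 as assuming independent patients. State the expected number of sites and restate the death-rate precision over a range of ICC values and site numbers.
- Report the population death rate with hospital-clustered standard errors.
- Add hospital to the minimum model for embedded regressions, as a random effect, fixed effects or cluster-robust errors. The choice can be left to each study's plan. Cluster-robust errors address only the standard errors, so an exposure partly set by local policy also needs a within-hospital comparison, for example through hospital fixed effects.
- Analyse hospital-level exposures such as volume with hospital as the unit of inference. Fixed hospital effects cannot be used there because they absorb the exposure.

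This changes wording and analysis only and should need no new data, provided the treating hospital is recorded. The stated precision becomes less favourable, and a few degrees of freedom are spent, costing about 0 to 6 points of power in the subgroup of 300 if hospital indicators are used.
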